## Methods/design

### Study design

The MLSE LaunchPad trial employs a single-arm, non-randomized within subject quasi-experimental design following a cohort of 350 participants aged 6–29 years old over up to 2-years of self-selected participation in programming at MLSE LaunchPad, a Sport for Development facility in downtown Toronto, ON, Canada. Data collection methods utilize repeated measures of age-specific outcomes according to hypotheses outlined in Table 1 and further described in Table 3 using self-reports and pedometer data at baseline, 6 months, 12 months, and 24 months from baseline. Qualitative assessments will take place annually throughout the data collection period using focus groups with a subset of participants. This protocol was developed in the fall of 2016 and initiated in February 2017. These data will collectively be used to evaluate the effects of intentional sport programming in a community hub on PYD and SFD outcomes in urban youth facing barriers. Moderating variables including age, gender, race, household income, postal code, program type, volume of participation and duration of participation will be explored to understand possible explanatory individual and programmatic elements of significance.

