### Study population

#### Inclusion criteria

Participants will be eligible for the study given the following criteria upon enrolment for the study:
Age 6–29 yearsRegistered member of MLSE LaunchPadAttending programming at MLSE LaunchPadAbility to speak, understand and read EnglishPhysically able to participate in programming with or without the use of assistive devices-Recruited within 8 weeks of commencing program participation.

MLSE LaunchPad defines ‘youth facing barriers’ as ‘youth who may need greater supports and services to reach their full potential’, including low income, racialized, Indigenous, new to Canada, LGBTQ2S, and homeless or underhoused youth; youth in care or leaving care; and youth in conflict with the law. Demographic data will be collected in self-report surveys and through member registration and used to define characteristics of the population. No formal process is used to ensure youth accessing MLSE LaunchPad’s programs meet the stated criteria for ‘youth facing barriers’, and no youth are excluded from programming based on these criteria; however, the neighborhood demographics and outreach strategy have to date resulted in program participation by youth who meet the criteria outlined.

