#### Recruitment

Recruitment of participants began in February 2017 and will continue through September 2019. Participants will be followed for up to two years with data collection to conclude by March 31, 2020. During program registration and within the first week of each program cycle, new participants (and parents/guardians if applicable) will be given information about the research study and the requirements of research participation. If the participant indicates interest, they (and the parent/guardian where applicable) will be taken through the consent process.

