19–29	Plus Sport Program Partners • NPower Canada – Classroom-based technical support professional training program that runs 5 half-days/week for 10 weeks with an on-court sport and activity component for 1 h/day 2 days/week • Covenant House – Kitchen-based hospitality placement training program that runs 5 full days/week for 8 weeks with an on-court sport and activity component for 1 h/day 2 days/week Open Gym (Sport Plus) • Unregistered semi-structured sport program • Participant-directed learning that is supported by a coach to develop intrinsic motivation and autonomy, general movement skills, and participant-selected movement and/or sport skills	Increased employment, apprenticeship, or training placement Increased rate of participation in sport or physical activity	Self-report of placement in job, apprenticeship, or training full- or part-time Self-report of regular sport/physical activity participation All outcomes are also assessed through scheduled qualitative data collection
All Ages	Events • One-time events providing specific demographic groups with novel experiences with specific intended outcomes, such as: - Empowering Girls through Sport - Kyle Lowry/Adidas event - Michael B. Jordan appearance - Community Celebration days (facility launch and anniversary celebrations) - Toronto Maple Leafs Prospect Camp - Toronto Maple Leafs “Next Gen” game - Toronto Maple Leafs and Toronto Raptors viewing parties - Basketball clinics - 3 on 3 basketball tournaments - MLSE game experiences Drop-in Counselling • Drop-in counselling with Child and Family Therapists • Therapists are available several hours each week in an on-site Wellness Room Snack Program • Fresh after-school snacks are provided 3 days/week for participants and their families	Outcomes relate to age-specific outcomes identified above	n/a

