Programs for the 6–12 and 13–18 year-old cohorts will be delivered in 8-week cycles with 5 cycles each year. As research participants may participate in multiple recreational programs concurrently, volume (total program hours) and duration (number of program weeks) of participation will be used as mediating variables in analyses to examine the dose-response on objectives outlined in Table 1. All programs will include life skills development using coaching strategies discussed by Camiré et al. (2011) [19], focused on 7 life skills identified in the MLSE LaunchPad Theory of Change: grit, resilience, self-esteem, self-regulation, critical thinking, social competence, and leadership.

Participants aged 19–29 years will be offered plus sport programming developed in collaboration with local community organizations offering occupational skills training and other employment services. These agencies will demonstrate strong histories of positive youth impact and will work with MLSE LaunchPad’s sport programmers to deliver integrated employment training and sport/physical activity programming. The addition of sport and physical activity is expected to offer a different context for reiteration of in-class themes (i.e. leadership and other key life skills) and to encourage increased long-term physical activity participation. The priority of this age group will be the Ready for Work pillar. Secondary emphasis will be on the Healthy Body and Healthy Mind pillars. Due to the training nature of these programs, the format will differ from the programs offered for youth aged 6–18, and programs will generally be delivered for 4 or more hours per day, 5 days per week for 8–10 weeks, with sport programming delivered in 1-h sessions 2 days/week.

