#### Outcomes

Participants will complete a baseline assessment within 2 weeks of recruitment. Follow-up research assessments will take place at 6 months, 12 months, and 24 months from the baseline assessment with data collection concluding March 31, 2020. Outcomes have been identified based on the program theory illustrated in the MLSE LaunchPad Theory of Change (See Fig. 1). Outcomes and indicators for the primary objectives are detailed in Table 3.

**Table 3 Tab3:** Outcomes for Primary Objectives

Participants aged 6–12	
a) Increased physical literacy	Indicator:
	PLAYself Physical Literacy Assessment for Youth [36] 22-item graded self-report scale used to evaluate level of physical literacy
b) Physical activity minutes/day	Indicator:
	One-week pedometry producing at least 3 days of valid data with a minimum wear time of 10 h/day
c) Continued engagement in sport	Indicator:
	Self-report of regular sport/physical activity participation
Participants aged 12–18	
a) Life skills:	Indicator:
i. Critical Thinking ii. Resilience iii. Self-esteem iv. Self-regulation v. Social Competence vi. Grit	Critical Thinking in Everyday Life Scale [37] 20-item self-report Likert scale used to measure use of critical thinking skills including reasoning, enquiry, analysis/information processing, flexibility, and evaluation Child & Youth Resilience Measure [38] 12-item self-report scale used to measure ability to sustain well-being Rosenberg Self Esteem Scale [39] 10-item self-report Likert scale used to assess global self-esteem Motivation and Self-Regulation Subscale; derived from the School Attitudes Assessment Survey [40] 4-item self-report Likert scale used to measure ability to initiate and continue behaviours required to achieve academic goals Social Competence Scale for Teenagers [41] 9-item self-report scale used to measure positive social skills necessary to get along well with others and function constructively in groups Grit Scale [42] 8-item self-report scale used to measure stamina in dimensions of effort and interest
b) Academic Performance:	Indicator:
i. School Attendance ii. Academic Performance iii Academic Attainment	Self-report of number of missed school days over past two weeks measured as a percentage GPA as per last report card; failed courses marked as “R” on TDSB report cards will be input as 45% Self-report of highest grade/level completed
c) Physical Outcomes	Indicator:

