i. Physical activity minutes/day ii. Health Behaviours iii. Continued engagement in sport	One-week pedometry producing at least 3 days of valid data with a minimum wear time of 10 h/day Healthy Behaviour Questionnaire 6-item, author-designed scale used to measure behaviours relating to sleep, nutrition, physical activity, smoking, substance use, and risky sexual behaviour Self-report of regular sport/physical activity participation
Participants aged 18–29	
a) Employment	Indicator:
i. Employment Status ii. Personal Income	Self-report of placement in job, apprenticeship or training; full- or part-time Self-report of personal income level
b) Sport Participation	Indicator:
i. Continued engagement in sport	Self-report of regular sport/physical activity participation

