*Ages 13–18:* Repeated measures ANOVAs will be used to examine the main effect of time on positive health behaviours and each of the six life skills, controlling for demographic variables such as age, gender, household income and race. Moderation analyses will be used to explore the impact of program dosage on the relationship between time and each of the six life skills. Pearson’s product-moment correlation coefficients will also be used to explore the relationship between each of the life skills, positive health behaviors and academic outcomes. Logistic regression will be used to identify predictors of high school graduation for the subset of this age group that would be expected to graduate during the study with possible predictors including scores for each life skill at 2-year follow-up, program dosage and program type, while controlling for gender, household income, housing status and baseline life skills score. The same variables will also be used in a standard multiple regression to identify predictors of continued participation in sport and physical activity in this age group.

*Ages 19–29:* Repeated measures ANOVAs will be used to examine the main effect of time on rate of employment, apprenticeship, or continued training, personal income, and rate of continued participation in physical activity, controlling for demographic variables such as age, education level, household income at baseline and housing status at baseline. Logistic regression will be used to identify predictors of employment status at 2-year follow-up, which may include program type and program dosage (number of programming hours), while controlling for similar demographic variables as identified above for the Repeated Measures ANOVA.

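### Ages 19–29: baseline job status and income are normally recorded during job training and follow-up comes after it, so the main effect of time cannot be read as a program effect

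*Protocol article*

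**What the plan says.** Under Study design, the protocol article describes a "single-arm, non-randomized within subject quasi-experimental design", so there is no comparator.

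The timing of baseline follows from three sections. The inclusion criteria require that the person is already attending programming and is "Recruited within 8 weeks of commencing program participation". The Recruitment section has staff inform people about the study at an early point: "During program registration and within the first week of each program cycle, new participants". The Outcomes section adds: "Participants will complete a baseline assessment within 2 weeks of recruitment". Follow-up is at 6, 12 and 24 months from baseline.

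For ages 19–29, Core programming states that "programs will generally be delivered for 4 or more hours per day, 5 days per week for 8–10 weeks". Table 2 lists two registered courses. One is technical-support training on 5 half-days a week for 10 weeks. The other is a "Kitchen-based hospitality placement training program that runs 5 full days/week for 8 weeks". Open Gym, which is unregistered, is also offered to this age group.

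Table 3 gives two employment indicators. The first is self-reported placement in a job, apprenticeship or training, full- or part-time. The second is "Self-report of personal income level", with no reference period. The planned test is "Repeated measures ANOVAs will be used to examine the main effect of time on rate of employment, apprenticeship, or continued training, personal income", adjusted for demographic variables such as age, education, and baseline household income and housing status. Table 1 attributes increases in placement and in personal income to participation.

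**The concern.** A within-person comparison needs a baseline that represents the person's usual state before the intervention. Here the intervention itself occupies much of the working week at the moment the reference value is recorded, and that constraint has gone by the first follow-up. People may also enter job training because they are out of work. Either mechanism could put paid work and current income below their usual level at baseline, and either would resolve without any benefit from the program. The covariates named as examples include no earlier work or personal-income history that could separate these explanations.

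Placement and personal income are two of the three primary hypotheses for this cohort. A change in either could be reported as impact when it reflects only the timing of the baseline. This is narrower than the general absence of a control group: it concerns the choice of reference value, and it can be improved within the single-arm design.

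**Working it through.** **1. The plan's own figure.** The Sample size section gives 100% post-hoc power for employment status at n = 150 and a large effect. Taking large as d = 0.8 (stated only for ages 6–12) and two-sided alpha 0.05 (assumed), a paired t-test has noncentrality 0.8 × √150 = 9.80 and power above 99.99%. The figure reproduces, but it says nothing about whether a change over time is caused by the program.

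**2. Where baseline falls.** Usual case: approach at registration or in week 1, plus up to 2 weeks, gives about weeks 0–3 of an 8–10 week course. Latest case: 8 + 2 = week 10, at or after the end of a course. The first follow-up, 6 months (about 26 weeks) after baseline, is past the end of the course attended at baseline in every case.

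**3. Direction depends on the outcome.** Assumptions: half the cohort is in training, the usual job rate is 40%, no trainee holds a job during the course, all trainees count as placed, nobody is in training at follow-up, and the program has no effect. These are deliberately extreme.
- Paid work: baseline 0.5 × 0 + 0.5 × 0.40 = 20%; follow-up 40%; change +20 points.
- Composite including training: baseline 0.5 × 1 + 0.5 × 0.40 = 70%; follow-up 40%; change −30 points.

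The same timing raises one measure and lowers the other.

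**4. Illustrative size for paid work.** Suppose half the cohort is in training, 20% of trainees work during the course and the usual rate is 40%. Baseline is then 0.5 × 20% + 0.5 × 40% = 30%, and full recovery takes it to 40%. Assume a latent within-person correlation of 0.2, n = 150 and no program effect.
- Variance of the paired difference = 0.30 × 0.70 + 0.40 × 0.60 − 2 × 0.0274 = 0.395, where 0.0274 is the covariance implied by the latent correlation.
- Standard error = √(0.395/150) = 0.0513; z = 0.10/0.0513 = 1.95.
- Probability of a significant rise = P(Z > 1.96 − 1.95), about 49%. Simulation gives 48–49%.

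With half the recovery (30% to 35%): variance 0.385, standard error 0.0506, z = 0.99, probability about 16%. With no dip, the rate in this direction is about 2.5%.

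**5. Illustrative size for income.** The article gives no income mean or SD, so the dip is expressed in SDs of the within-person change. A paired t-test at n = 150 finds a rise in 23%, 68% and 95% of trials for dips of 0.1, 0.2 and 0.3 SD, again with no program effect.

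Only n = 150 and the timings come from the article. All rates, shares, correlations and dips are assumed. The n = 150 is the recruitment target, and fewer people will contribute paired data.

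**The case against.** The strongest reply has four parts.

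- **The job outcome counts training.** A trainee may already score as placed at baseline, so the rate could start high and fall. This stands. A reader might infer that both placement and income would be falsely confirmed; the documents do not support that for placement, where the direction is open.
- **A temporary low is not shown.** The article reports no baseline employment or income. Its definition of youth facing barriers includes homeless or underhoused youth, youth leaving care and youth in conflict with the law, so low employment may be the usual level for some, with nothing to return to. Half-day training leaves room for part-time work, Open Gym users need not be in training, and some baselines fall at the very start or the end of a course. This also stands: a dip is possible, and its size cannot be derived from the article.
- **Income depends on item wording.** If the item asks about annual income, a dip of a few weeks largely disappears. The article does not give the wording, so the income concern is conditional on a current-period item.
- **The single-arm design is openly declared.** That is true, but declaring the design does not stop the time effect from being read as impact, as the wording of the hypotheses invites.

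The simulated outcome, paid work alone, is not one the plan analyses as such. The calculation shows how sensitive a paired test is to a modest recovery; it does not estimate the error rate of this trial.

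**Conclusion.** The point holds in limited form. For participants in the registered courses, the reference value is normally taken during training and every comparison value after that course ends. The main effect of time therefore cannot separate a program effect from the end of training and re-entry to work. Upward bias is plausible for paid-job holding, and for personal income if the item is current-period. For the composite that includes training, the bias may be downward.

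The size is unknown. Under the assumed rates, a 10-point recovery in paid work gives a false positive in about half of trials at n = 150, and a 5-point recovery in about 16%. It would be too strong to say that the cohort starts at a temporary low or that a false rise is to be expected. This is an interpretive weakness in a primary analysis that should be corrected, but with size and, for placement, direction unknown, it ranks below a must-fix defect.

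**What to change.** 1. Add two or three questionnaire items on paid work and personal income before program entry, with a stated reference period, and ask the follow-up items over the same period. People already enrolled can answer the pre-entry items at their next visit.
2. Report paid work separately from apprenticeship and training, and do not count the facility's own course as placement at baseline.
3. In the analysis for ages 19–29, present change against the pre-entry level alongside change from the in-training baseline.
4. State in the same section that a rise over the in-training baseline alone will not be read as a program effect on employment or income.

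The cost is a few items in an existing electronic questionnaire and some added text. The pre-entry level should not become the sole reference. It carries recall error, which is larger for those already enrolled, and the pre-entry period may itself include the low point that led people into training. Showing both comparisons makes that uncertainty visible but does not replace a comparator.

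### The 2-year employment regression for ages 19–29 does not name employment at entry as a covariate, so its program-type and dose effects may be confounded, by an amount and in a direction the protocol cannot fix

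*Protocol article*

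**What the plan says.** Under Data analysis, the paragraph for ages 19–29 sets out two analyses of employment. One is a repeated-measures ANOVA on time. The other is a predictor model: "Logistic regression will be used to identify predictors of employment status at 2-year follow-up, which may include program type and program dosage (number of programming". Dose is thus a count of hours. The model's controls are given by reference, "while controlling for similar demographic variables as identified above for the Repeated Measures ANOVA", and the ANOVA's list reads "controlling for demographic variables such as age, education level, household income at baseline and housing status at baseline". Employment at entry is not named in either place.

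The surrounding sections fix the context:

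- **Inclusion criteria.** These cover age, membership, attendance, English, physical ability and timing of recruitment. None concerns employment.
- **Study design.** The study has a single arm, participation is self-selected, and the outcomes are measured at baseline, 6, 12 and 24 months.
- **Outcomes, Table 3.** Employment status is "Self-report of placement in job, apprenticeship or training; full- or part-time". A baseline value is therefore collected.
- **Core programming.** For this cohort "programs will generally be delivered for 4 or more hours per day, 5 days per week for 8–10 weeks".
- **Intervention, Table 2.** The other regular program for this age group is "Open Gym (Sport Plus) • Unregistered semi-structured sport program".

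**The concern.** The model's outcome is a status at one time point, not a change. With no control arm and self-selected exposure, covariate adjustment is its only protection against confounding. A person's employment at entry plausibly predicts employment two years later. It also plausibly affects which program that person can or wants to attend. A job seeker is the natural user of a weekday training course, while someone already working has less room for it and may only drop in to Open Gym. If so, Sport Plus and low hours would partly mark youth who were already working.

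This model bears on the cohort's lead outcome and on the secondary hypothesis that volume and duration of participation correlate positively with the primary outcomes. Confounding by entry employment could hide a real benefit of training, make training look harmful, or, if the imbalance ran the other way, create an apparent benefit.

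**Working it through.** **1. Is entry employment covered by the stated covariates?** The list is open-ended in wording but is limited to demographic variables, and the four examples do not include the participant's own employment. For comparison, the regressions for ages 6–12 name the baseline physical literacy score among the predictors of change in physical literacy, and baseline activity level among the predictors of change in activity. The authors thus name the outcome's baseline value elsewhere, but not for ages 19–29. The graduation model for ages 13–18 also names a baseline score, but that is the baseline of a predictor, so it is a weaker comparison.

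**2. How different are the doses?** The minimum course hours are 4 × 5 × 8 = 160 to 4 × 5 × 10 = 200. Anyone who completes a course sits far along the hours scale, so program type and dose will be closely linked.

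**3. How large could the bias be?** The protocol has no figure to reproduce here. Its stated power for employment status gives no employment rates. Every rate below is an assumption.

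Let e_T and e_G be the shares employed at entry among training and Open Gym participants. Let q1 and q0 be the chances of employment at 2 years for those employed and not employed at entry. With no program effect:

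- p_T = e_T·q1 + (1 − e_T)·q0, and likewise p_G from e_G
- unadjusted OR = [p_T/(1 − p_T)] / [p_G/(1 − p_G)]

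*Scenarios set by uptake* (q1 = 0.85, q0 = 0.50):

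- Strong imbalance: 40% employed at entry, training taken up by 5% of the employed and 80% of the others. e_T = 0.02/0.50 = 0.04 and e_G = 0.38/0.50 = 0.76. p_T = 0.514 and p_G = 0.766, so OR = 0.32.
- Milder: 20% employed at entry, uptake 30% and 50%. e_T = 0.06/0.46 = 0.13 and e_G = 0.14/0.54 = 0.26. p_T = 0.546 and p_G = 0.591, so OR = 0.83.

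*Scenarios set by entry employment*, true OR = 1, with three levels of persistence:

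| Employed at entry, training vs Open Gym | q1/q0 = 60/50% | 75/50% | 85/45% |
|---|---|---|---|
| 20% vs 20% | 1.00 | 1.00 | 1.00 |
| 15% vs 30% | 0.94 | 0.86 | 0.79 |
| 10% vs 40% | 0.89 | 0.74 | 0.61 |
| 5% vs 60% | 0.80 | 0.57 | 0.40 |
| 30% vs 15% (reversed) | 1.06 | 1.16 | 1.27 |

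Across both sets the unadjusted OR runs from 0.32 to 1.27 with no true effect. If the true conditional OR is 2.0, the 10% vs 40% row becomes 1.77, 1.45 and 1.19. Over the whole grid a true 2.0 appears as anything from 0.78 to 2.35. Conditioning on entry employment recovers the true value, but only because the scenarios contain no other confounder.

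**4. When is entry status measured?** Recruitment may fall up to 8 weeks after programming starts, and the baseline assessment up to 2 weeks later: 8 + 2 = 10 weeks. Courses last 8–10 weeks. A baseline self-report can therefore come during or after a course. Because the outcome counts training as a placement, attending the facility's own course could itself register as placed at entry.

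**The case against.** A reader might infer that the program-type and dose effects will mainly reflect who was already working. The documents do not support that. They give no entry employment rate, no persistence of employment and no link between entry employment and program type. With equal entry employment there is no confounding, and with a reversed imbalance the bias changes sign.

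Other points on that side also carry weight:

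- The idea that working youth seldom attend the courses is inference. One of the two named courses runs on half-days, so a part-time worker could attend.
- Occupational training is the core offer for this age group. Nothing shows that Open-Gym-only participants form a sizeable comparison group.
- The regression is exploratory, meant to inform programming, and program type and hours are named only as possible predictors.
- Baseline household income and education would absorb part of the confounding, and the illustration ignores both.
- The open covariate wording leaves entry employment unnamed rather than ruled out, and an analysis plan may add it.
- It would be too strong to say that youth employed at entry cannot improve. Full- or part-time status is recorded, and personal income is a separate outcome.

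These points limit how much can be said about size and direction. They do not remove the gap: the article does state the class of covariates for this model, and the baseline value of the outcome lies outside it although it is collected. Household income and education are only partial stand-ins for a person's own job.

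**Conclusion.** The point holds as a confounding gap in one model. Youth already in work can enter, exposure is self-selected, and the covariates named for the 2-year employment regression leave out employment at entry. The effects of program type and hours may therefore be confounded, plausibly against the training courses. The illustrative range of about 0.3 to 1.3 for a true odds ratio of 1 rests wholly on assumed rates. It shows that the bias could matter, not that it will.

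The repeated-measures ANOVA on time is not affected, because baseline is its first time point. The change is worth making because it is specific and nearly free.

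**What to change.** In the Data analysis paragraph for ages 19–29, name paid employment at entry as a covariate in the 2-year employment logistic regression, and state that the facility's own training course does not count as a placement for this variable. Use status before programming began where it is available, since a later baseline could already reflect the course and adjusting for it would remove part of any program effect. The article does not say whether member registration records employment, so this needs checking. Where only the baseline self-report exists, say so.

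Reporting the result among participants not in paid work at entry is an optional sensitivity analysis. Enrolment does not change. The cost is one more model parameter and, if the optional table is reported, a subgroup smaller than the planned 150.

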We hypothesize that a) volume of participation and b) duration of participation will correlate positively with the primary outcomes listed above.

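### In the 19–29 cohort, employment at 2 years is regressed on programming hours that may accrue after placement, so the outcome can affect the dose and bias its effect in either direction

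*Protocol article*

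**What the plan says.** - **Model.** Data analysis (ages 19–29): a logistic regression is planned for "predictors of employment status at 2-year follow-up, which may include program type and program dosage (number of programming hours"). The predictors named are thus program type and dosage, and the wording on them is tentative. The covariates are demographic: age, education, baseline household income and baseline housing status are the examples given. Neither baseline employment nor the time of placement is named.
- **Dose.** Core programming: "volume (total program hours) and duration (number of program weeks) of participation will be used as mediating variables in analyses". This follows a sentence on the two younger cohorts but refers to the objectives in Table 1, which cover all three.
- **Who sets the dose.** Study design: "self-selected participation in programming at MLSE LaunchPad", for up to two years, in a single arm.
- **Hypothesis.** Table 1, secondary hypotheses: "volume of participation and b) duration of participation will correlate positively with the primary outcomes listed above". Placement in work, apprenticeship or training is one of those outcomes for this cohort.
- **Programs.** Core programming: "programs will generally be delivered for 4 or more hours per day, 5 days per week", for 8–10 weeks. Besides the two training courses, the regular program that Table 2 lists for this age band is Open Gym: "Unregistered semi-structured sport program", with no fixed length.
- **Success.** Table 3 counts a training place, full- or part-time, alongside a job or apprenticeship.

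**The concern.** The outcome is read at month 24 and the exposure can keep growing until month 24, past the event that it is meant to predict. For a participant placed in month 5, the 19 months of possible attendance that follow are part of the dose, and having a job may shape them. None of the named covariates removes this.

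The structure of the programs makes it matter more here than in the younger cohorts. Training hours depend mainly on which course was taken and whether it was finished. With program type in the model, much of the remaining variation in hours is attendance after training, the part most open to influence from employment.

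At stake is the dose-response hypothesis for this cohort. The Background section says that the regressions are meant to guide programming, so a dose coefficient of the wrong sign or size could be used to cut or expand programs on false grounds.

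**Working it through.** **1. The plan's own figure.** Sample size states 100% power for employment status with n = 150 and a large effect. With d = 0.8 and an assumed two-sided alpha of 0.05, power = Φ(d√n − 1.96) = Φ(0.8 × 12.25 − 1.96) = Φ(7.84), above 99.99%. The figure reproduces, but it has no bearing on this point, which concerns the direction of causation and not precision.

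**2. Hours at issue.** From Core programming, training is at least 4 h × 5 days = 20 h/week, so 160 h over 8 weeks and 200 h over 10. After week 10, 104 − 10 = 94 weeks remain. Open Gym at an assumed average of 0.25–1 h/week would add 23.5–94 h. This is large enough to matter against the spread in training hours.

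**3. Simulation with no true effect.** Inputs from the article: n = 150, a 10-week course of 200 h, follow-up to week 104. Assumptions: 60% employed at 24 months; mean course completion 0.85 (170 h); Open Gym averaging 0.25, 0.5 or 1 h/week; placement at a uniform random time between weeks 10 and 104; no job loss; a given share of placed participants stop attending at placement. Model: logistic regression of employment on total hours/50.

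| Share of placed who stop | OR per 50 h | Significantly negative |
|---|---|---|
| None | about 1.0 | 2–3% |
| A quarter | 0.85–0.94 | 4–12% |
| Half | 0.73–0.86 | 21–37% |
| All | 0.49–0.67 | 64–93% |

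The nominal rate in the last column is 2.5%. Adding program type, with two courses of different hours, leaves the bias: at half stopping, OR 0.77–0.87 and 21–32%.

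**4. A second, different model.** This used weekly job entry, job loss and program exit, with Open Gym at 0 or 2 h/week; all rates are assumed. With no true effect, the OR per 100 total hours is 0.99–1.05 if employment leaves attendance unchanged, and 0.56–0.84 if employed people drop 50–100% of their hours. With a truly beneficial dose, the OR is 1.16–1.28 if attendance is unchanged, and 0.72–1.03 if employed people drop 50–100%.

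**5. How many reach 24 months.** Recruitment runs from February 2017 to September 2019 (32 months) and data collection ends 31 March 2020. A 24-month visit needs a baseline by 31 March 2018. With baseline within two weeks of recruitment, that leaves about 13.5 months of recruitment. Under even recruitment (an assumption), 13.5/32 = 42%, and 0.42 × 150 ≈ 63. At n = 63 the simulation in step 3 gives a significantly negative result in 30–58% of trials if all stop and 10–16% if half stop. The smaller number lowers the rate of significance but does not remove the bias.

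**6. The opposite direction.** A participant who is on a second training course at follow-up has more hours and, under Table 3, could be counted as placed. That pushes the association upward. It was not simulated, because the article gives no basis for how often it would occur.

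**7. Does a cut-off cure it?** In the second model, using hours in weeks 1–10 among those not yet employed at week 10 gives OR 0.91–1.04 per 100 h with no true effect (0–2% significantly negative), and 1.15–1.40 with a true benefit. In the first model, one scale for everyone, or a landmark at course end, gives OR about 1.0 with 1–3% significantly negative.

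**The case against.** A reader might infer that getting a job does make participants leave, and that the model will therefore show programming as harmful. The article does not support that. It nowhere reports attendance after placement, and with no stopping the bias in steps 3 and 4 vanishes. Some of the text points the other way: Wrap-around services presents drop-in programs as suitable for youth who cannot commit to registered ones, which would fit people in work, and Incentivization rewards attendance. The Table 3 definition of placement means that even the sign is not settled. These objections stand, and they limit the point to a conditional one.

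It can also be said that the regression is exploratory, since its predictors only may include dose, and that the accrual window of a covariate belongs in an analysis plan. The first part lowers the severity. However, dosage is one of only two predictors named, and a positive dose-response is a stated hypothesis. The second part stands only in part: the article does more than leave a window open. It describes the dose as total hours of self-selected participation, and that definition is unsuitable for this outcome as it stands.

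**Conclusion.** The point holds in conditional form. As defined, programming hours in the 19–29 model can be partly a consequence of employment, and no named covariate corrects for it. If a quarter to all of the placed participants stop attending, a program with no effect yields an odds ratio per 50 hours between about 0.94 and 0.49. If none stop, it is about 1.0. If further training is counted as placement, the error can go upward. The employment rate, placement times, Open Gym hours and, above all, the stopping rate are assumptions, so the figures show a possible range and are not a forecast. Significant results would be rarer than the n = 150 figures suggest, because far fewer participants can reach 24 months. This is a secondary analysis with an inexpensive remedy. It should be changed, but it does not undermine the study as a whole.

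**What to change.** In Data analysis (ages 19–29), replace total hours by a dose that employment cannot alter:

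- **Training-course participants.** Use one scale for everyone. Either (a) hours attended divided by hours offered, up to the earlier of placement or the scheduled end of the first course; or (b) hours during the first course, among those not yet placed at its end (a landmark analysis).
- **Open Gym-only participants.** Use hours in the same fixed early window.
- **Model.** Use this dose to predict later employment, adjust for baseline employment status, and do not count training at the facility itself as a placement in this model.
- **Reporting.** Describe later hours without modelling them, and record the date of first placement.

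The single scale is essential. If hours were used for most participants and a 0–1 proportion only for those placed during the course, early successes would receive a near-zero dose. With no true effect, n = 150 and 10% of the employed placed early, that gives an OR of about 0.58 per 50 h and a significantly negative result in about 60% of trials.

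**Cost.** A reworded definition that uses attendance data already collected centrally, and one added questionnaire item. The dose range becomes narrower and later Open Gym hours no longer count.
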